#### Goniometry

A standard 6-in plastic goniometer will be used to measure active forearm supination and pronation as well as wrist flexion, extension, and radial and ulnar deviation. To measure AROM of the finger and thumb MCP and IP joints, a flat metal finger goniometer will be used. Active forearm rotation will be measured by stabilizing the participant’s elbow at his/her side with the elbow flexed to a 90° angle. Active radial and ulnar deviation motion will be measured by placing the participant’s hand palm down on the tabletop or if forearm pronation is limited the participant will rest his/her elbow on the tabletop. Active wrist flexion and extension as well as digital motion will be measured with the participant’s elbow on the tabletop in a hand up position. AROM measurements of the digits will be recorded as total active motion (TAM) calculated in a standard manner described by American Society for Surgery of the Hand using formula below [29].$$\mathrm{Finger\ TAM }= (\mathrm{MP\ flexion }+\mathrm{ PIP\ flexion }+\mathrm{ DIP\ flexion}) - (\mathrm{MP\ extension\ deficit }+\mathrm{ PIP\ extension\ deficit }+\mathrm{ DIP\ extension\ deficit})$$$$\mathrm{Thumb\ TAM }= (\mathrm{MP\ flexion }+\mathrm{ IP\ flexion}) - (\mathrm{MP\ extension\ deficit }+\mathrm{ IP\ extension\ deficit})$$

#### Dynamometry

Grip strength will be measured using a Jamar™ dynamometer with the handle position set on the second notch while the participant is seated with his/her elbow flexed to 90° and stabilized beside the side of the body as recommended by the American Society of Hand Therapists [30]. Therapist B will ask the participant to squeeze the handle as hard as he/she can for 3 s while the reading is being obtained. The grip strength test will be performed three times beginning with the non-affected hand then alternating to the affected hand. Participants will be advised not to exceed their comfort level and not to cause pain when squeezing with their affected hand. For participants who are not able to generate any force with their affected hand, 0 kg will be recorded. The grip strength score is the average of three trials for each hand recorded in kilograms.

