### Eligibility criteria {10}

The inclusion criteria are patients with (1) lower-third of the forearm extra-articular, partial articular, and/or complete articular individual or combined fractures of the radius, ulna or distal radioulnar, and/or radiocarpal joint, (2) fracture(s) stabilized with ORIF technique within 2–4 weeks of referral, and (3) the ability to read and communicate in English. The exclusion criteria include (1) diagnoses of rheumatoid arthritis, multiple limb or body fractures, carpal fracture/injury, or associated peripheral nerve or tendon injury, and (2) patients with a history of cognitive or psychological impairment. For this RCT, there is no age limit to participate; however, if there is a large variance in age, sub-analysis will be performed.

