### Recruitment {15}

All patients with lower-third forearm fractures stabilized by ORIF, who are referred to Occupational Therapy between 2–4 weeks after ORIF and meet the inclusion criteria will be recruited.

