## Statistical methods

### Statistical methods for primary and secondary outcomes {20a}

All data will be analyzed using the IBM Statistical Product and Service Solutions (IBM SPSS). Descriptive analysis for categorical data such as gender, marital status, hand dominance, type of wrist fracture, and educational level will be expressed in frequency, percentage, and proportion. Descriptive statistics will be used to analyze continuous data including age, Quick-DASH score, PRWE score, IES-R score, PPT score, AROM of the forearm and wrist, TAM for the digits, and grip strength. These results will be expressed as mean, standard deviation, minimum and maximum if the data is normally distributed or as median and interquartile range. If the data is not normally distributed, sub-analysis will be conducted to determine the outlier and the outlier will be extracted from the data set if it shows significant influence. A mixed model ANOVA will be used to test the primary outcome of this study by evaluating the mean difference between and within groups of the Quick-DASH scores obtained at baseline and after the 12th therapy session. The difference in the initial and final PRWE score, IES-R score, PPT score, AROM of the forearm and wrist, and TAM of the digits and grip strength will be analyzed using a mixed model ANOVA. Depending on the results of the aforementioned analyses, other sub-analysis will be performed as necessary.

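### Grip in kilograms is tested with no covariate, although the uninjured hand is measured at the same visit and could recover power for this secondary outcome

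*Protocol article*

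**What the plan says.** The Dynamometry section of the protocol article measures both hands: "The grip strength test will be performed three times beginning with the non-affected hand then alternating to the affected hand". It sets the scale: "The grip strength score is the average of three trials for each hand recorded in kilograms". Effort on the injured side is limited: "Participants will be advised not to exceed their comfort level and not to cause pain when squeezing with their affected hand". A floor value is provided for: "For participants who are not able to generate any force with their affected hand, 0 kg will be recorded".

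Baseline is taken before the first therapy session, in patients "who are referred to Occupational Therapy between 2–4 weeks after ORIF and meet the inclusion criteria will be recruited" (Recruitment). On the spread of patients, the eligibility section says that "there is no age limit to participate; however, if there is a large variance in age, sub-analysis will be performed", and it has no sex restriction.

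For the analysis, Statistical methods for primary and secondary outcomes says that "TAM of the digits and grip strength will be analyzed using a mixed model ANOVA", applied to initial and final values. It lists no covariate, gives the other hand no role, and does not say which hand's score is tested. Grip is a secondary outcome and is named in hypothesis (3). The sample size rests on the Quick-DASH alone.

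**The concern.** With two groups and two time points, the group-by-time test in a mixed ANOVA is the same test as a t-test on change. A change score removes stable differences between people only to the extent that the baseline value carries them. Soon after fixation, with a comfort-limited squeeze, injured-hand grip may say little about how strong the person normally is. By the final visit, grip in kilograms again scales with normal strength. A strong person and a weak person who both regain half of their normal grip then show very different kilogram changes.

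That variation goes into the error term. With men and women of any age among about 34 evaluable patients it could be large, and a null grip result would be harder to interpret. The measurement that would account for it, grip of the uninjured hand, is already taken at baseline.

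**Working it through.** **The plan's own figure.** For the Quick-DASH, with f = 0.25, alpha 0.05, correlation 0.5 and two measurements, the interaction test has noncentrality f²·N·m/(1 − ρ) = 0.0625 × 34 × 2/0.5 = 8.5 on 1 and 32 degrees of freedom. Power is 0.807 at N = 34 and 0.795 at N = 33, so 34 reproduces. Then 34/0.9 = 37.8, which rounds up to 38. Nothing below affects this figure, and no power is claimed for grip.

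**Inputs for grip.** The documents give none, so all of these are assumptions:
- 17 evaluable per arm (34 split equally);
- uninjured grip U: mean 30 kg, CV 30% (SD 9 kg);
- injured hand as a fraction of U: baseline 0.12 (SD 0.08), final 0.50 (SD 0.15), correlation 0.4;
- craft gain of 15 or 10 percentage points at the final visit;
- alternative baseline fraction 0.35.

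**Variance of the kilogram change.** Change = U × c, where c is the change in fraction.
- Var(c) = 0.15² + 0.08² − 2 × 0.4 × 0.15 × 0.08 = 0.0193.
- Var(U·c) = 30² × 0.0193 + 9² × mean(c)² + 9² × 0.0193 = 17.37 + 81 × mean(c)² + 1.56.

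The middle term is normal strength passing into the change score. It grows as the baseline fraction falls, because mean(c) is then larger.

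**Baseline 12%, gain 15 points.** mean(c) is 0.38 in control and 0.53 in intervention.
- Unadjusted: variances 30.6 and 41.7, average 36.2, SD 6.01 kg. The effect is 30 × 0.15 = 4.5 kg. Noncentrality = (4.5/6.01) × √(17/2) = 2.18, giving power of about 56% on 32 df.
- With U as covariate: the middle term drops out except for a slope difference of 81 × 0.075² = 0.46. Variance is 19.4, SD 4.40 kg, noncentrality 2.98, power about 82% on 31 df.

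**All three settings.** The formula ignores truncation at 0 kg and error in the reference hand. The simulations allow for truncation and take 5% reference error.

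| Baseline, gain | Unadjusted kg: formula / simulation | Covariate: formula / simulation |
|---|---|---|
| 12%, 15 points | 56% / 58% | 82% / 82% |
| 12%, 10 points | 31% / 33% | 49% / 47% |
| 35%, 10 points | 43% / 45% | 49% / 50% |

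With no true effect, rejection stays near 5% with and without the covariate.

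**A second model.** Assumptions: men 40 (SD 8) kg, women 25 (SD 5) kg, half men, 10-point gain, final-fraction SD 15 points unless varied. Here the covariate analysis is ANCOVA on kg with affected-hand baseline and uninjured-hand grip.
- Baseline at 5, 15, 25 and 35% of the uninjured hand: unadjusted 26, 32, 39 and 43%; covariate 42, 47, 49 and 47%.
- Women only: 40% against 46%.
- Final-fraction SD 8 points: 44% against 90%. SD 20 points: 24% against 30%.
- Adjusting for affected-hand baseline alone, at 15%: 33%, almost no gain on 32%. The gain comes from the other hand.

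**The case against.** The strongest reply has four parts.

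1. **The premise is not documented.** No baseline grip mean, SD, share at 0 kg or sex mix is given. The 0 kg sentence is a recording rule for people who produce no force and does not describe the typical patient. This stands. A reader might infer that injured-hand baseline grip is near the floor, but the documents support only that it may be low. At 35% of the uninjured hand the gain falls to about 4 or 5 points.

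2. **Unadjusted kilograms are valid.** This also stands. A reader might infer that the planned analysis hides a treatment effect. It does not bias the estimate or distort the false-positive rate; it can only lose precision, on one of several secondary outcomes. For a 10-point gain, the adjusted test at about 47% to 50% is still underpowered.

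3. **An analysis plan that is not shown may add the covariate.** This is possible. But the article does fix both the score and the test, and what it fixes leaves the other hand unused and the tested hand unnamed. The comment is on that stated choice. The planned sub-analysis for large age variance does not meet it: it is unspecified, and it concerns neither sex nor body size.

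4. **Percent of the uninjured hand is debatable.** Agreed. A reader might conclude that the ratio should replace kilograms, since it also gains power in these simulations. It ignores the difference between dominant and non-dominant hands and changes the scale of the outcome. The covariate obtains most of the gain while keeping kilograms.

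**Conclusion.** The point holds as a matter of efficiency. As written, the grip analysis leaves out a measurement already taken that could sharpen the comparison. The benefit depends on how weak the injured hand is at baseline and how widely normal strength varies, and neither is documented. With CV 30% and baseline at 12% of the uninjured hand, the covariate is worth about 24 power points for a 15-point gain (82 − 58) and 14 for a 10-point gain (47 − 33). With baseline at 35% and a 10-point gain it is worth about 5 (50 − 45). Adjustment did not lower power in any setting checked. The primary outcome, the sample size of 34/38 and the validity of the grip test are unaffected.

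**What to change.** In Dynamometry and in Statistical methods for primary and secondary outcomes:
- name affected-hand grip in kilograms as the tested outcome;
- add the uninjured hand's baseline grip as a prespecified covariate, for example in an ANCOVA of final affected-hand grip on group, affected-hand baseline and uninjured-hand baseline;
- report percent of the uninjured hand descriptively if wanted, without testing it.

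No new measurement is needed. The covariate costs one error degree of freedom (32 to 31), and a second if affected-hand baseline is also entered. The larger cost is that this is a late change: enrolment began in July 2021 and was expected to end in December 2023, and the Researcher is unblinded and has sole access to the data. The choice should therefore be fixed, dated and documented before the outcome data are analysed, with a statement that it was made without sight of results by group.

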### Plans to promote participant retention and complete follow-up {18b}

There are no plans to promote participant retention or to complete follow-up. Follow-up data will not be collected for participants who discontinue or deviate from intervention protocols.

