### Strategies to improve adherence to interventions {11c}

The Researcher will track participant attendance to ensure all therapy sessions are completed before Therapist B does the final assessment. If a participant fails to attend a session, the Researcher will phone the participant to reschedule within the timeframe of the study.

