### Relevant concomitant care permitted or prohibited during the trial {11d}

Participants will be allowed to consume any prescribed medication, including analgesics, during the study. If, however, analgesic consumption exceeds more than that prescribed while participating, this will be documented by Therapist A and the Researcher. Participants will be excluded if other Occupational therapy or Physiotherapy for the injured hand is initiated while participating in this 6-week study. During the study, Intervention group participants will be allowed to replicate the protocol craft-making activities at home.

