## Data collection and management

### Plans for assessment and collection of outcomes {18a}

Prior to the first therapy session, Therapist B will do the initial baseline assessment. During the assessment, each participant will be interviewed by Therapist B to obtain his/her demographic data and pertinent medical history. After obtaining this information, the outcome assessments related to disability, physical performance, and post-traumatic stress will be done. Therapist B will also do the 6-week reassessment after completion of the 12th therapy session.

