### Methods in analysis to handle protocol non-adherence and any statistical methods to handle missing data {20c}

Missing data will be replaced with the mean imputation method. Intention-to-treat analysis will be used for participants that are non-adherent.

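### Intention-to-treat is promised for non-adherent participants, but their final outcome is never collected, so the analysis is completers' data plus mean imputation under an intention-to-treat label

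*Protocol article*

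**What the plan says.** Five sections of the protocol article bear on who contributes a final score.

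- **{20c}, non-adherence and missing data:** "Intention-to-treat analysis will be used for participants that are non-adherent". It also states: "Missing data will be replaced with the mean imputation method". It does not say whether the mean is taken overall or within group.
- **{18b}, retention and follow-up:** "There are no plans to promote participant retention or to complete follow-up", followed by "Follow-up data will not be collected for participants who discontinue or deviate from intervention protocols".
- **{11c}, adherence:** attendance is tracked "to ensure all therapy sessions are completed before Therapist B does the final assessment". A participant who misses a session is phoned to rebook within the study period.
- **{18a}, assessment:** "Therapist B will also do the 6-week reassessment after completion of the 12th therapy session". This is the only assessment after baseline.
- **{11d}, concomitant care:** "Participants will be excluded if other Occupational therapy or Physiotherapy for the injured hand is initiated while participating in this 6-week study". The section does not say whether exclusion means from treatment, from the trial or from the analysis.

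**The concern.** Intention-to-treat protects a randomised comparison only if outcomes are sought from everyone randomised, including those who stop or depart from treatment. Here the analysis promise in {20c} and the data-collection rule in {18b} apply to the same participants and point in opposite directions. The primary outcome would be observed only in people who stayed with the protocol.

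At stake is the Quick-DASH comparison in a superiority trial of 38 people. If people doing badly are more likely to drop out, and more of them drop out of one arm, the observed means no longer compare like with like. Imputing a mean of observed scores carries that distortion into the analysis. The outcomes needed to judge its size would not exist.

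**Working it through.** **1. The sections side by side.**

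| Participant | Final score collected? | Treatment in the analysis |
|---|---|---|
| Completes 12 sessions | Yes ({18a}) | Observed value |
| Discontinues or deviates | No ({18b}) | Intention-to-treat, mean imputed ({20c}) |
| Starts other therapy for the hand | Excluded, scope unclear ({11d}); no final score if this counts as deviation or withdrawal ({18b}) | Not stated |
| Falls short of 12 sessions after rebooking | No assessment provided for ({11c}, {18a}) | Mean imputed ({20c}) |

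Every final score that carries information comes from the first row.

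**2. The plan's sample size reproduces.** Inputs from {14}: f = 0.25, two groups, m = 2 measurements, correlation ρ = 0.5, alpha 0.05, power 80%. The noncentrality is λ = f²·N·m/(1 − ρ) = 0.0625 × 34 × 2 / 0.5 = 8.5 on 1 and 32 degrees of freedom. Power is 0.807 at N = 34 and 0.781 at N = 32. Dropout: 34/0.9 = 37.8, so 38. The calculation therefore rests on 34 observed final scores. With 33, power is 0.795, so any loss beyond the anticipated four takes it below 80%.

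**3. Design effect on the SD scale.** With ρ = 0.5 the variance of a change score is 2(1 − ρ) = 1 in units of SD². For 17 per arm, λ = δ² × 17/2 = 8.5, so δ = 1.0 SD. That is the difference in change the trial is powered to detect.

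**4. What four losses can do.** Simulation with no true effect, 40,000 runs per row. With two time points, the group-by-time interaction in the planned mixed ANOVA is equivalent to a t test on change scores.

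- From the document: 38 randomised, 4 lost, ρ = 0.5, mean imputation of the final score.
- Assumed: 19 per arm, and log-odds of loss of 1 per SD worse final score.
- Varied: the split of losses between arms, and overall-mean versus group-mean imputation.

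Bias is craft minus control in SD units. A positive value means craft looks worse. Each cell gives overall-mean / group-mean imputation.

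| Lost: control / intervention | Bias (SD) | Two-sided type I error | False positives favouring craft (nominal 2.5%) |
|---|---|---|---|
| 2 / 2 | 0.00 / 0.00 | 0.049 / 0.061 | 2.5% / 3.1% |
| 3 / 1 | +0.09 / +0.10 | 0.058 / 0.071 | 1.2% / 1.7% |
| 1 / 3 | −0.09 / −0.10 | 0.058 / 0.070 | 4.5% / 5.5% |
| 4 / 0 | +0.17 / +0.20 | 0.082 / 0.102 | 0.7% / 0.7% |
| 0 / 4 | −0.17 / −0.19 | 0.080 / 0.102 | 7.4% / 9.3% |

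Repeats of the same set-up agree closely. The highest type I error seen for four losses in one arm was 0.107, and the highest false-positive rate for craft was 9.6%. In the 2/2 row, the excess under group-mean imputation comes from single imputation understating variance, not from bias.

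The worst rows shift the estimate by about a fifth of the 1.0 SD design effect. The article gives no SD for Quick-DASH, so this cannot be converted to points.

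**The case against.** The fair objections concern size and cause. The contradiction itself stands.

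- **Is it simply a per-protocol analysis?** A reader might conclude so. That goes too far, because mean imputation can nominally keep every randomised participant in the data set. The exact description is completers' outcome data with single mean imputation, labelled intention-to-treat.
- **Does loss differ by arm?** The article does not show it. The reasons one might offer pull in opposite directions: the intervention visit is 15 minutes longer, while controls know that they are not getting craft. Participants in both arms know their allocation ({17a}). The bias is a possibility the plan cannot rule out. It is not an established fact.
- **Does the plan inflate false claims of benefit?** Only if intervention participants who do badly are the ones lost. Loss of controls who do badly works against craft and cuts false positives for craft to under 1%. A balanced split gives almost no bias.
- **Does assessment after session 12 let the timing drift between arms?** This is tempting for a condition that improves with time. However, {11c} keeps rebooked sessions within the study period, other sections describe a 6-week study, and no between-arm delay or weekly rate of improvement is documented. I do not rely on it.
- **Does {11d} remove people from the analysis?** It may mean only withdrawal from treatment. The wording needs clarifying, and an analysis exclusion is not proven.
- **Could an unseen analysis plan settle this?** Not the core of it. The rule in {18b} governs data collection, and analysis cannot restore what was not measured.

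**Conclusion.** The point holds: {18b} and {20c} contradict each other, and {11c} and {18a} leave no route to a final score for anyone who does not complete 12 sessions. The unclear exclusion in {11d} adds to this. Confidence in the contradiction is high.

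The size of the harm is conditional. With four losses, 19 per arm, ρ = 0.5 and the assumed log-odds of 1 per SD, bias runs from about 0 (2/2 split, type I error 0.05–0.06) through 0.09–0.10 SD (3/1 split, about 0.06–0.07) to 0.17–0.20 SD when one arm bears all four losses (0.08–0.11). The direction depends on which arm loses its worse patients. False positives favouring craft reach roughly 7–10%, against a nominal 2.5%, only when all four losses are in the intervention arm. More than four losses could make this larger and would take power below 80%.

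It should be corrected because it concerns the primary outcome, the remedy is cheap, and the article reports recruitment as ongoing, so each further participant who deviates is a final score lost for good.

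**What to change.** - **{18b}:** replace the no-follow-up sentence with a rule along these lines: *Therapist B will assess every randomised participant at 6 weeks from baseline, within a stated window, regardless of sessions attended, deviation, discontinuation or other therapy, unless consent for follow-up is withdrawn. Self-report scales may be completed by phone or post if needed.*
- **{11d}:** state that participants who start other therapy are recorded and kept in the analysis as randomised. This concerns data and analysis only and changes no rule on treatment.
- **{11c} and {18a}:** align them so that the final assessment does not depend on 12 completed sessions.
- **{20c}:** report a completers analysis as sensitivity only.
- **Participants already lost without a final score:** report their number and reasons by arm, and do not use an unqualified intention-to-treat label.

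The cost is a short amendment and about four extra assessments or questionnaires at the anticipated loss. Including participants with fewer than 12 sessions will dilute the estimated effect slightly. Outcomes already missed cannot be recovered by the amendment.
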